### Concealment mechanism {16b}

Allocation will be concealed to prevent selection bias. Through a process of centralised allocation, schools will be recruited by Department for Education staff before allocation is determined. Once recruitment is complete, the allocation sequence will be generated by university staff using a project-specific school ID provided by the Department. University staff conducting the allocation will be blinded to school names to maintain impartiality. After allocation, the Department will match the project-specific school IDs to school names and subsequently inform the recruited schools of their assigned group (intervention or control). This process ensures that allocation remains concealed until assignments are finalised and communicated to the schools.

### Implementation {16c}

Randomisation will be undertaken by an independent member of Education Futures at the University of South Australia blinded to the school (cluster) names. All schools selected for participation will be randomised. Blinding at the student level will not be possible due to the pragmatic clustered design.

## Assignment of interventions: blinding

### Who will be blinded {17a}

Although random allocation will be undertaken blinded to school names or identifying details, post randomisation the study implementation cannot be blinded due to the clustered design. Outcome assessment will be undertaken by the Department and also not blinded. Analyses will be undertaken independently of the Department and the data analysts will be blinded to the allocation arm.

### Procedure for unblinding if needed {17b}

Participants are unblinded. Analysts will be blinded and unblinding will not be permissible for them.

## Data collection and management

### Plans for assessment and collection of outcomes {18a}

Assessment of self-regulated learning will be undertaken by the teacher of participants in grades 2, 4 and 6. For grades 4 and 6, the self-regulated learning assessment will additionally be self-completed by the student.

For all secondary outcomes (WEC and NAPLAN), data will be obtained from the Department for Education, South Australia. The WEC and NAPLAN are administered annually by the Department as part of standard practice. NAPLAN is typically conducted during the second full week of May each year in Australian schools. It is a nationwide assessment program used to measure the literacy and numeracy skills of students in grades 3, 5, 7, and 9. The exact timing of the Wellbeing and Engagement Collection (WEC) collection can vary from year to year, but generally takes place during the second term (April to July) of the school year. The WEC is administered to all schools that have agreed to participate (approximately 90% of all South Australian government schools). For the schools that do participate all students from grade 4 through to 12 will be requested to complete the survey.

### Plans to promote participant retention and complete follow-up {18b}

A requirement of the school recruitment will include a commitment to facilitate all data collection for the purposes of the RCT and to participate in the NAPLAN and WEC data collections. All students have a unique Education ID that transfers with them should they change schools. As such participating students will be tracked through the education system with data linked and made available to researchers.

The greatest risk to long-term follow-up data will be for the grade 6 students who in year 7 will transition from primary to high school. Approximately 10% of students transfer to the private education sector during this transition and will likely be lost to longer-term follow-up. It is not expected that this loss would differ across the control and intervention groups.

### Data management {19}

Much of the data will be collected via administrative data linkage on the basis of the student’s Education ID. Where trial-specific data collection is required, all will be conducted by trained assessors, whom have experience working in school settings. Assessors will have at least a bachelor’s level education. Data collection will be overseen by the Study Coordinator, however, will be collected and linked by the Department for Education. Once extracted and provided to the University the research team will be responsible for cleaning, coding security and storage as consistent with the University’s and ethical requirements. All analyses will be undertaken by the research team, independent of the Department for Education.

### Confidentiality {27}

Student-level data will never be received by the research team in an identified format. Students will be uniquely identified by their Education ID, so will remain known to the Department, but not the research team. Similarly, schools will be uniquely identified in all records by their school ID.

### Plans for collection, laboratory evaluation and storage of biological specimens for genetic or molecular analysis in this trial/future use {33}

N/a as no biological specimens will be collected.

## Statistical methods

### Statistical methods for primary and secondary outcomes {20a}

The primary analysis will use the intent-to-treat principle. Baseline balance will be checked between trial arms to see whether randomisation was successful. Estimation of treatment effects will be obtained from a generalised linear mixed model (GLMM) to produce the mean difference in scores for SRL intervention versus control. The GLMM will include a random effect for a cluster, and a random effect for the child taking account of the repeated measure design, a fixed effect for time, and use an exchangeable correlation structure of the appropriate variance–covariance matrix. The same analytical approach will be applied to secondary outcomes of interest. Longitudinal data collected for school cohort participants will be linked using student Education IDs. Student household characteristics may serve as predictors of interest in adjusted analyses.

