#### Covariates

Covariates will be obtained through linked education administrative data and will include the geographical socio-economic status of the primary residence of the child, parent's highest level of education, measures of reading abilities (as an indicator of pre-intervention cognition), disability status, school card status (poverty indicator), and prior school attendance records.

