### Sample size {14}

A sample of (at least) 56 schools will be required with at least one class in grade 2, grade 4 and grade 6, with an average cluster size of 19 children/class to detect a minimum impact of 0.25 SD effect size on the primary outcome with (at least) 80% power while accounting for the clustered design with an intraclass correlation coefficient (ICC) of 0.05. This results in a total sample of (at least) 56 clusters with an estimated 3192 students (or 1064/year level).

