## Assignment of interventions: allocation

### Sequence generation {16a}

Schools will be the level of randomisation and class the level of implementation. Randomisation will be stratified by socio-economic status blocks (using the Socio-Economic Indexes for Areas (SEIFA) indicator [29]) and metropolitan vs. non-metropolitan areas. The allocation sequence will be generated using computer-generated random numbers in Stata. Specifically, three block randomisation lists, one for each SES stratum will be generated with block sizes of 4 to ensure balanced allocation within each stratum. The advantage of numerous classes within the one school grade level has limited advantage for sample power due to the design effect associated with clustering. As such, at least one class per eligible grade level will be randomly selected for the intervention. Teachers will implement the intervention at the class level. The trial will be powered to assess the impact of the SRL intervention on three grades independently: grade 2 (early primary), grade 4 (mid primary), and grade 6 (late primary). The intervention will be implemented in literacy/reading lessons. Class lists will be provided by each of the participating schools for the process of randomisation. Note that schools in the treatment group may decide to implement the SRL intervention in more than one class within the school; however, only selected classes will be enlisted for the study. Schools in the control group will be required to not use the intervention (not even for non-enlisted classes).

We note that more than the required sample of 56 schools may wish to participate. As such we consider 56 as the minimum sample size, however the resultant study may be larger. Additionally, schools not meeting the eligibility criteria may still wish to participate in the study, for example, rural schools with multigrade classes. For such schools, we will include them as additional samples and block randomise accordingly.

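### The primary mixed model as listed omits the randomisation strata and leaves baseline adjustment optional: precision is given up for nothing and the test is conservative if the strata predict the rating

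*Protocol article*

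**What the plan says.** In the protocol article, the section on statistical methods for primary and secondary outcomes {20a} begins with intention to treat and then states: "Baseline balance will be checked between trial arms to see whether randomisation was successful". The treatment effect is to come from a generalised linear mixed model with a random effect for cluster, a random effect for child and a fixed effect for time. The arm is implied, because the model must yield a mean difference. No stratification factor or baseline covariate is listed. The section ends: "Student household characteristics may serve as predictors of interest in adjusted analyses".

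Sequence generation {16a} says "Randomisation will be stratified by socio-economic status blocks" and adds metropolitan versus non-metropolitan location. It then describes three lists, one per socio-economic stratum, in blocks of four. The section on concomitant care {11d} adds stratification on a 2024 waitlist for an existing support programme.

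The Covariates paragraph under Outcomes {12} commits to obtaining area socio-economic status, parental education, "measures of reading abilities (as an indicator of pre-intervention cognition"), disability, school card status and prior attendance. The Discussion says that socio-economic status and reading ability will be considered in the analyses, without saying in which model.

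**The concern.** There are two separate effects.

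- **Omitted strata.** Stratified allocation removes between-strata differences from the sampling variation of the treatment estimate. A model without the strata still counts those differences as residual variation between schools. Its standard error is then larger than the true one, the interval is too wide and the test rejects too rarely under the null.
- **Omitted covariates that were not stratified on.** The interval stays valid, but precision is lost that data already being linked could supply. A chance imbalance between 28 and 28 schools also goes uncorrected in the primary estimate.

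The balance check does not repair either effect. With computer-generated, centrally concealed allocation of schools, a sound randomisation can still leave arms that differ by chance. Looking at baseline differences is therefore a poor way to decide whether randomisation worked, and it does not change the estimate.

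**Working it through.** **Inputs from the protocol** (Sample size {14} and Abstract): the design is meant "to detect a minimum impact of 0.25 SD effect size on the primary outcome with (at least) 80% power", "accounting for the clustered design with an intraclass correlation coefficient (ICC) of 0.05", with 19 children per class and 56 schools allocated 1:1, each grade treated as its own trial. **Assumed:** two-sided 5% significance, which the sample size section does not state, and every share of variance explained, since the protocol gives none. Calculations use school means for one grade at one time point, not the full repeated-measures model.

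**1. The plan's own figure.** Without clustering, 252 children per arm are needed. The design effect is 1 + 18 × 0.05 = 1.9, so 252 × 1.9 = 478.8 per arm, and 478.8 / 19 = 25.2 schools per arm. That gives 52 schools by the normal approximation, or 54 by a t-test on school means. With the planned 28 per arm:

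SE = √(2 × [0.05 + 0.95/19] / 28) = √(2 × 0.100 / 28) = 0.0845.

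Power for 0.25 SD is 84.1% (normal) or 82.8% (t, 54 df). The claim of at least 80% holds without any adjustment.

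**2. Strata left out.** Let R be the share of between-school variance explained by the strata. The true variance of a school mean under stratified allocation is 0.05(1 − R) + 0.05, while the model without strata uses 0.100. The SE is overstated by the factor √(0.100 / [0.05(1 − R) + 0.05]), and the type I error is 2[1 − Φ(1.96 × that factor)].

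Power comes from a simulation with 56 schools in six assumed strata, blocks of four, 20,000 null runs and 8,000 runs at 0.25 SD.

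| R (assumed) | SE overstated by | Type I error, formula | Type I error, simulated | Power without strata | Power with strata |
|---|---|---|---|---|---|
| 0 | 0% | 5.0% | 4.9% | 83.1% | 82.9% |
| 0.10 | 3% | 4.4% | 4.1% | 83.3% | 84.5% |
| 0.25 | 7% | 3.6% | 3.6% | 84.4% | 87.7% |
| 0.50 | 15% | 2.4% | 2.4% | 86.1% | 92.3% |

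At R = 0.10 the simulated 4.1% is probably a little low by chance: in the same runs the correctly adjusted test rejected 4.6% of the time rather than 5%. Power forgone is about 1, 3 and 6 points at R = 0.10, 0.25 and 0.50.

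**3. Strata and covariates together.** Let both levels of variance shrink by the same share R:

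SE = √(2 × [0.05(1 − R) + 0.95(1 − R)/19] / 28), with 5 df spent on strata.

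- R = 0.10: SE = √(2 × 0.090 / 28) = 0.080, power 86.4%.
- R = 0.25: SE = √(2 × 0.075 / 28) = 0.073, power 91.7%.

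The comparator is 82.8% with no adjustment and no benefit from stratification. Where the strata matter, stratified allocation has already raised unadjusted power (84.4% at R = 0.25 in the table), so the gain from changing the model is somewhat smaller than the plain difference.

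**The case against.** The strongest reply is that this is a condensed article and that an analysis plan not shown may specify strata and covariates. The list of model terms is clearly not exhaustive, since it does not even name the arm. The Discussion also foresees that socio-economic status and reading will be considered. This stands in part: it would be wrong to say that the trial ignores covariates. But the article does more than stay silent. It lists the primary model's terms and places household characteristics in optional adjusted analyses, and an analysis plan that followed this text would treat a stratified trial as unstratified.

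The size is also open to challenge. The outcome is a teacher rating with one class per grade and school, so between-school variation includes differences in how teachers rate, which the strata need not explain. That stands, and the loss may be near zero.

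A reader might infer three stronger points that the text does not support.

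- **Significance tests of baseline balance.** The text says that balance will be checked and names no test or threshold. Rates of spurious failure, such as 1 − 0.95⁶ = 26% for six independent 5% tests, would describe a procedure that the protocol does not contain.
- **A useless check.** Recruitment {15} describes class selection after the randomisation of schools, and opt-out consent. In a cluster trial, differences can enter at such steps, so looking at baseline data has some diagnostic value. The fault is in using it as a verdict on randomisation.
- **Intervals too wide throughout.** That holds only for omitted strata. Omitting other covariates costs precision, not validity.

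**Conclusion.** The point holds as a shortfall in how the primary model is fixed, and not as an error that invalidates the trial. As listed, the model leaves out the stratification factors, and adjustment for data already to be linked is optional and tied to no primary estimate. The direction is certain if strata predict the rating: standard errors are too large, the test is conservative and power is lost. The size cannot be derived from the protocol. Under the assumed shares of 10% to 50% of between-school variance, type I error falls to between 4.4% and 2.4%, and about 1 to 6 points of power are forgone. With strata and covariates explaining 10% or 25% at both levels, power would be about 86% or 92%, against 83% with no adjustment. It would be too strong to conclude that the trial is underpowered: the stated 80% is reached with or without adjustment, and any error in the test is on the cautious side.

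**What to change.** In section {20a}:

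1. Make the primary estimate adjusted. Include as fixed effects the stratification factors actually used, plus a short set of pre-intervention covariates such as prior reading and prior attendance. Name the set before outcome data are seen and keep it whatever the baseline table shows.
2. First settle what the strata are. Section {16a} names socio-economic status and metropolitan location but describes lists by socio-economic stratum only, and section {11d} adds the waitlist.
3. Report the unadjusted estimate as a sensitivity analysis.
4. Replace the sentence on whether randomisation worked with a descriptive baseline table by arm.

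The cost is wording, since the covariates are already to be linked and the stratification factors are known at randomisation. There are two small downsides. Missing covariate values need a simple, stated rule. A few degrees of freedom are also spent, which costs about 0.2 points of power if the strata explain nothing (83.1% against 82.9% in the simulation).

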**Methods:**

We will use a standard pragmatic clustered (by school) randomised controlled superiority trial with an additional population-wide matched parallel control arm. Effectively, we will conduct three trials—one for each age/grade level. Each trial will be powered to assess the impact of the intervention on the age/grade groups independently: grade 2 (early primary, 7–8 years), grade 4 (mid primary, 9–10 years), and grade 6 (late primary, 11–12 years). Schools assigned to the treatment group will have all three grade levels (grades 2, 4, and 6) receiving the treatment (at least one class per grade); no classes in the schools assigned to the control group will receive the intervention. A minimum of 56 schools with an average cluster size of 19 children/class will be required to detect a minimum impact of 0.25 SD effect size at 80% power taking into account the clustered design with an intraclass correlation coefficient (ICC) of 0.05. This results in a total sample of 1064 per grade and thus 3192 students in total (56 schools per arm × 19 students in an average-sized class × three grade levels). Randomisation will occur on a 1:1 ratio, such that half of the schools (*n* = 28), and effectively about half of the students (*n* = 1596) will receive the intervention. The primary outcome will be improved self-regulation assessed at 6 weeks, 6 months and 12 months post the intervention. Longer-term secondary outcomes will include academic and wellbeing measures obtained through administrative data linkage to the National Assessment Program in Literacy and Numeracy (NAPLAN) outcomes and the Wellbeing and Engagement Collection (WEC) outcomes measures in the year following implementation (grades 3, 5, and 7). Follow-up via the South Australia Data Linkage Systems will allow for longer-term academic outcomes, mental health, school completion, criminal justice, and tax data.

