### Outcomes {12}

#### Primary outcome

The primary outcome will be the student’s Self-Regulated Learning at 6 months post-implementation of the intervention, as assessed by the student’s teacher using a brief rating scale consisting of 14 items.

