#### Secondary outcomes

Self-regulated learning will also be measured by the brief teacher-rated scale at 6 weeks and a student self-report measure with the same items will be utilised for grades 4 and 6. The student instrument will be implemented at 6 weeks, 6 months and 12 months post the intervention. Standardised academic achievement tests, Wellbeing and Engagement Collection (WEC) domains [27], school engagement, attendance and behaviour data will be obtained from the Department for Education through administrative data linkage.

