### Participant timeline {13}

Socialisation of the trial will be undertaken from November 2023, with school recruitment occurring at the same time. In the third school term, all intervention resources will have been fully adapted to the Australian context and modified to be appropriate for the three different grade levels.

Each of the four school terms is approximately 10 weeks. The teacher training will ideally be implemented late in the first term. The intervention will commence in all treatment schools across the three different grade levels in term 2 2024 (commences 29th April). We will provide video-based tutorials prior to each lesson of the intervention to remind teachers about the specific contents. Ideally, the intervention will be delivered from weeks 3 to 9 in terms 2, with flexibility given due to teacher sickness or other unforeseen disruptions.

Limited trial-specific measurements will be collected pre and post-intervention to ensure as low a burden on the school system as possible. Where possible, all data pertinent to the trial will be collected via administrative data collection. Depending on the assessment these are collected at different times of the year and for different grade levels. Trial participants will be linked to the Department’s administrative data systems with a longitudinal data set linked and generated for analyses. Extractions from the Department systems will occur once per term post-completion of the intervention, with impact determined on the different outcomes as the students age into and thus complete the various outcomes of interest (Fig. 1).

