The primary objective of the trial is to adapt and implement the SRL intervention in Australian primary schools, assess its effects on self-regulated learning skills, and evaluate the intervention’s cost-effectiveness for potential scale-up in South Australia. Our primary outcome is a teacher-reported assessment of student’s self-regulated learning skills at 6 months after the intervention’s implementation. We selected this as the primary outcome measure, as it represents the earliest indication of the intervention’s impact. This measure is crucial for establishing whether any subsequent improvements in academic outcomes are attributable to enhanced self-regulated learning, rather than direct improvements in literacy and reading instruction. This assessment will be conducted near the end of the school year, before students move into different classes with new teachers, making it the latest feasible time point for evaluation. We acknowledge that teachers are not blinded to the trial arm due to the study design, which may introduce potential reporter bias. However, alternative methods, such as independent student observation or task-based assessments, were not considered to be feasible given the large sample and concerns from the Department for Education regarding the additional burden on teachers and students. The trial will also examine secondary outcomes, including academic achievement, attendance, behavioural problems, and various well-being domains. The study will involve a sample of at least 56 schools, with an average cluster size of 19 children per class, resulting in a total sample size of approximately 3192 students across three grade levels. Data will be collected through teacher-rated scales, administrative data linkage to educational outcomes, and the Wellbeing and Engagement Collection. Covariates, such as socioeconomic status and reading abilities, will also be considered in the analyses.

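### As written, the repeated-measures model gives one intervention effect averaged over visits, while the primary outcome is the effect at 6 months

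*Protocol article*

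**What the plan says.** Under Outcomes {12}, the primary outcome is the teacher-rated "Self-Regulated Learning at 6 months post-implementation of the intervention". The Discussion repeats that time point ("self-regulated learning skills at 6 months after the" intervention) and defends it as the last feasible assessment before pupils move to new teachers. The 6-week teacher rating is a secondary outcome: "Self-regulated learning will also be measured by the brief teacher-rated scale at 6 weeks".

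Statistical methods {20a} describes a generalised linear mixed model "to produce the mean difference in scores for SRL intervention versus control". Its listed terms are a random cluster effect and "a random effect for the child taking account of the repeated measure design, a fixed effect for time", and it will "use an exchangeable correlation structure of the appropriate variance–covariance matrix". The section mentions neither an arm-by-time interaction nor a 6-month contrast, and it does not limit the primary analysis to 6-month data. No other section supplies any of these.

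The Abstract gives a different primary time frame: "The primary outcome will be improved self-regulation assessed at 6 weeks, 6 months and 12 months post the intervention". Specific hypotheses lists the same three times for the teacher rating.

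**The concern.** A child random effect that allows for repeated measures means that more than one visit per child is in the model. With arm and time as main effects only, the model assumes the same intervention effect at every visit and returns one number for all of them. A visit that the protocol calls secondary then carries the same weight as the primary one.

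This matters if the effect changes over time, which is plausible here. The intervention lasts five weeks, and the raters are unblinded teachers, a source of bias that the Discussion acknowledges. An early rise in ratings that has gone by 6 months could be reported as a positive primary result. Conversely, an effect that takes time to build would be understated.

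**Working it through.** **Inputs from the protocol** (Abstract; Sample size {14}): 56 schools allocated 1:1, so 28 per arm; 19 pupils per class; ICC 0.05; target effect 0.25 SD; at least 80% power. **Assumed:** two-sided alpha 0.05; total variance 1; within-child correlation r = 0.6 (school 0.05, child 0.55, residual 0.40); complete data; one class per school within a grade. The effect patterns below are illustrations and are not taken from the protocol.

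**The plan's own figure.** Without clustering, n per arm = 2(1.96 + 0.842)²/0.25², which rounds up to 252. The design effect is 1 + 18 × 0.05 = 1.9. Then 252 × 1.9 = 478.8 pupils, and 478.8/19 = 25.2, so 26 schools per arm (52 in total). With t critical values it is 27 per arm (54). At 28 per arm, power is 84.1% (normal) or 82.8% (t). The stated 56 schools therefore meet the stated power. This is a calculation for a single time point.

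**What the arm coefficient estimates.** Arm is constant within a school. With complete data and an exchangeable structure, the main-effects model returns the plain mean of the visit-specific arm differences. An expected generalised least squares calculation confirmed this:

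| Visits modelled | True effects | Arm coefficient, no interaction | 6-month contrast with arm-by-time |
|---|---|---|---|
| 6 weeks, 6 months | 0.25, 0.10 | 0.175 | 0.10 |
| 6 weeks, 6 months | 0.40, 0.25 | 0.325 | 0.25 |
| 6 weeks, 6 months | 0.25, 0 | 0.125 | 0 |
| 6 weeks, 6 and 12 months | 0.35, 0.25, 0.05 | 0.217 | 0.25 |
| 6 weeks, 6 and 12 months | 0.40, 0.25, 0.10 | 0.25 | 0.25 |
| 6 weeks, 6 and 12 months | 0.25 throughout | 0.25 | 0.25 |

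In the last two rows the two estimates agree, once by coincidence and once because the effect is constant.

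**Standard errors.** For k visits averaged, the variance of a school mean is 0.05 + [(r − 0.05) + (1 − r)/k]/19, and SE = √(2 × variance/28).
- k = 1: variance 0.05 + 0.95/19 = 0.100, SE 0.0845
- k = 2: variance 0.05 + 0.75/19 = 0.0895, SE 0.080
- k = 3: variance 0.05 + 0.683/19 = 0.0860, SE 0.078

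**Probability of a significant result**, two visits, normal approximation:
- Effects 0.25 then 0: averaged 0.125/0.0799 = 1.56, giving about 35%. The 6-month contrast gives 5%. With r = 0.4 or 0.8 the averaged figure is 36% or 33%.
- Effects 0.40 then 0.10: averaged 0.25/0.0799 = 3.13, giving about 88%. The 6-month contrast is 0.10/0.0845 = 1.18, giving about 22%.
- Effects 0 then 0.25 (late onset): averaged again 0.125, about 35%. The 6-month contrast is 0.25/0.0845 = 2.96, giving about 84%.

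**The case against.** The strongest reply is that the list of terms is not exhaustive. The treatment arm is not listed either, although it must be in the model, so silence on arm-by-time does not exclude it. The section also speaks of treatment effects in the plural and applies the same approach to secondary outcomes. Reporting a 6-week secondary result beside a 6-month primary one calls for an estimate at each visit. The analysis plan, which is not shown, may name the contrast. All this stands as a limit: a reader might infer that the protocol rules out a 6-month estimate, and it does not. But the protocol does write out a model and a single output, and an analyst following that text would obtain a visit average. That goes beyond detail left for later.

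It is also fair that the two estimates coincide under a constant effect, and that the set of modelled visits is unsettled, since the Abstract and Specific hypotheses add 12 months. The size of any gap therefore cannot be fixed from the documents.

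Two stronger readings are tempting but unsupported.
- A reader might infer that a pre-intervention rating enters as a repeated row, diluting a constant 0.25 to (0 + 0.25 + 0.25)/3 = 0.167. Participant timeline {13} says only "Limited trial-specific measurements will be collected pre and post-intervention". It does not name the self-regulation scale or say how such a measurement would be coded, and the covariate list has no baseline rating.
- A reader might infer that a class-within-school effect is wrongly omitted. The protocol describes in effect three grade-specific trials with one class per grade per school, so school and class coincide within each grade. It writes no model that pools grades, and separate grade estimates can be compared without one.

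**Conclusion.** The concern holds in this form: followed as written, the model in Statistical methods {20a} estimates an effect averaged over visits, and nothing in the protocol ties it to the 6-month outcome set in Primary outcome and the Discussion. The mismatch follows from the text. Its size does not: the 35% against 5% depends on the chosen effect pattern, on two visits being modelled and on two-sided alpha 0.05, but little on the within-child correlation (33% to 36% over 0.4 to 0.8). The illustration shows what the wording would allow. It does not show that the trial's result will be wrong. Because the wording determines the primary estimate, it should be settled before the data are analysed.

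**What to change.** In Statistical methods {20a}, specify fixed effects for arm, time (categorical) and arm-by-time. State that the primary estimate in each grade is the model-based arm difference at 6 months, and take the 6-week difference from the same model as a secondary result. Fitting the primary model to the 6-month ratings alone would also do. State which teacher-rating visits enter the model, and bring the Abstract and Specific hypotheses into line with Primary outcome and the Discussion on the primary time point.

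Two conditional notes could be added. If a pre-intervention rating is used, enter it as a covariate or constrain it to be equal across arms. If a model pooling grades is fitted, add a class-within-school random intercept.

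The cost is a few lines of text and a standard error of about 0.0845 in place of 0.080, roughly 6% wider. The sample size is unaffected, because its calculation already rests on the single-visit standard error of √(2 × 1.9/(28 × 19)) = 0.0845.
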